**Early Anti-SARS-COV-2 Convalescent Plasma in Patients Admitted for COVID-19 Infection: A Randomized Phase II Trial**

Trial registration ClinicalTrials.gov Identifier: NCT04375098

After the study had begun, we adapted the protocol to add troponin and pro-BNP plasma level determination into the patient follow-up.

**Objectives**

General objective:

To evaluate the efficacy and safety of early convalescent plasma therapy on the progression of COVID-19.

Specific objectives:

- To study the efficacy of convalescent plasma in preventing COVID-19 clinical progression, comparing immediate plasma administration versus administration only at respiratory failure development or prolonged hospitalization.
- To study the safety of convalescent plasma in hospitalized patients with COVID-19.
- To determine the effect of convalescent plasma in the SARS-CoV-2 clearance rate in hospitalized patients with COVID-19.

**Study Design**

Prospective, single center, parallel-group, open-label randomized trial.

**Setting**

Medical unit of a Chilean academic tertiary center.

**Population**

**Inclusion criteria**

(1) Patients over 18 years old

(2) Hospitalized with COVID-19 symptoms present at enrolment and confirmed with a positive SARS-CoV-2 real-time polymerase chain reaction (RT-PCR) in nasopharyngeal swab

(3) COVID-19 symptoms ≤ 7 days to enrolment

(4) A CALL prediction score ≥ 9 points at enrolment* ^1^

(5) Eastern Cooperative Oncology Group (ECOG) performance status before SARS-CoV-2 infection 0-2.

**Exclusion criteria**

(1) PaO2/Fi O2 less than 200 or need for mechanical ventilation at enrolment

(2) Coinfection with other potentially relevant respiratory pathogen on admission

(3) Pregnancy or lactation

(4) Known IgA Nephropathy or IgA deficiency

(5) Previous intravenous immunoglobulin or plasma administration within the last 60 days

(6) Previous transfusion reactions that justify plasma contraindication (e.g. severe allergy)

(7) Do not resuscitate indication

(8) Patients participating in another interventional study related to COVID-19

(9) Patients that under investigator criteria had any condition that makes them unsuitable for study participation.

* CALL score includes the following parameters: age (< or > 60 years old), lymphocyte count (< or >1000), LDH (≤ 250; 250-500; >500) and comorbidities. The following comorbidities are included in the original CALL score: hypertension, diabetes, cardiovascular disease, liver disease, asthma, chronic lung disease, HIV infection and malignancy for at least 6 months. We added to comorbidities obesity (BMI≥ 30), chronic renal failure (stage III-V), solid organ transplant (<6 months) or hematopoietic transplant (<1 year), and immunosuppressant or immunomodulators use. We specified HIV infection with CD4<200 and cancer under current systemic treatment or in advance stage (IV).

CALL score is intended to predict the risk of developing severe COVID-19 defined as: SaO2≤ 93%, tachypnea ≥30 rpm, PaO2/FiO2 ≤ 300 o mechanical ventilation. Probability of progression to respiratory insufficiency is <10% for a CALL score 4-6, 10-40% for a CALL score 7-9 and >50% for a CALL score 10-13 (PPV 15.1; NPV 0.57) [20].

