**Randomization**

Eligible patients will be randomly assigned via computer generated numbering by a block randomization sequence into two groups: early or deferred plasma transfusion. Randomization will be done by an independent member and sequence will be concealed to study investigators.

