**Intervention and comparison**

The early plasma group will receive convalescent plasma on the day of enrolment. The deferred plasma group will receive convalescent plasma only if a prespecified worsening respiratory function criterion is met during hospitalization (Pa02/Fi02 <200) or, if the patient still requires hospitalization for symptomatic COVID-19 >7 days after enrolment.

The transfusion will consider a total of 400 mL of ABO compatible convalescent plasma, constituted by two 200 mL units separated by 24 hours. Plasma will be administered at a rate of 100 mL/h with close clinical monitoring. In both groups cointerventions including antibiotics, antivirals, heparin thromboprophylaxis, and immunomodulators such as steroids and tocilizumab will be allowed under the institutional protocol.

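### Entry spans the CALL severe line on PaO2/FiO2, but neither the randomisation nor the primary test takes baseline oxygenation into account

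*Combined protocol and SAP*

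**What the plan says.** - **Entry by risk score.** The inclusion criteria require "A CALL prediction score ≥ 9 points at enrolment". The footnote under the exclusion criteria lists the components: "CALL score includes the following parameters: age (< or > 60 years old), lymphocyte count (< or >1000), LDH" and comorbidities. None of them measures oxygenation.
- **What the score predicts.** The same footnote states: "CALL score is intended to predict the risk of developing severe COVID-19 defined as: SaO2≤ 93%, tachypnea ≥30 rpm, PaO2/FiO2 ≤ 300" or ventilation.
- **What is excluded.** The only respiratory exclusion is "PaO2/Fi O2 less than 200 or need for mechanical ventilation at enrolment".
- **Objective.** The first specific objective is "To study the efficacy of convalescent plasma in preventing COVID-19 clinical progression". It compares immediate plasma with plasma held back until respiratory failure or a long stay.
- **The trial's own failure line.** Under Intervention and comparison, the deferred group receives plasma "only if a prespecified worsening respiratory function criterion is met during hospitalization (Pa02/Fi02 <200"), or if still in hospital with symptomatic disease more than 7 days after enrolment. Secondary Outcomes uses the same value of 200 for respiratory failure.
- **Randomisation.** "Eligible patients will be randomly assigned via computer generated numbering by a block randomization sequence into two groups". No stratification factor and no block size are given.
- **Analysis.** The SAP tests the primary composite by chi-squared or Fisher's exact test. Logistic regression adjusting for age, SOFA and any imbalanced, clinically significant baseline variables is labelled exploratory. The planned subgroup analyses are immunological only.

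**The concern.** A patient with PaO2/FiO2 anywhere from 200 to 300 passes the exclusion and already meets the footnote's definition of severe disease. The score cannot filter such patients out, because it contains no oxygenation item. The trial therefore enrols across a wide band of baseline oxygenation.

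Baseline PaO2/FiO2 is likely to be strongly prognostic here. It is on the same scale as the trial's failure line, and a patient at 210 starts much closer to that line than a patient above 300. The documents give no figure for the strength of this relation.

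In 58 patients, unstratified blocks leave the split between the two states to chance, and the unadjusted primary test does not remove any imbalance that arises. What is at stake is some power, and how readily the headline odds ratio can be interpreted if the arms happen to differ at baseline.

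**Working it through.** **Inputs from the documents.** 29 per arm, 58 in total; primary event rates 54.8% and 20%; power 80%; two-sided 5% (Sample Size; SAP).

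**Assumed inputs, not in the documents.** The share of patients with PaO2/FiO2 ≤300 at entry, and the difference in primary risk between the two states.

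**1. The plan's own sample size.** Pooled formula, with mean rate 0.374:

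n = [1.96·√(2·0.374·0.626) + 0.842·√(0.548·0.452 + 0.20·0.80)]² / 0.348² = 29.1, which rounds up to 30.

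With 55% against 20% (the 35-point reduction as stated) the same formula gives 28.8, hence 29. The plan's 29 is reproduced. Power at 29 per arm is 79.8%.

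**2. Chance of imbalance.** If K of the 58 are severe, the number X in one arm of 29 is hypergeometric: P(X = x) = C(K, x)·C(58−K, 29−x) / C(58, 29). The gap in severe share is |2x − K| / 29.

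| Assumed share | K | P(gap ≥10 points) | P(gap ≥20 points) |
|---|---|---|---|
| 20% or 80% | 12 or 46 | 33.1% | 10.3% |
| 30% or 70% | 17 or 41 | 56.5% | 8.2% |
| 40% or 60% | 23 or 35 | 59.2% | 10.6% |
| 50% | 29 | 60.0% | 11.4% |

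The gap in patients has the same parity as K. A gap of 20 points (0.20 × 29 = 5.8 patients) therefore needs 6 patients when K is even and 7 when K is odd. Over every whole number from 12 to 46, the last column runs from 5.6% to 18.9%.

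**3. What such a gap does.** Shift in the arm difference = gap × risk difference between states. For 6 patients (6/29 = 20.7 points):

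- assumed risks 45% and 65%: 0.207 × 0.20 = 4.1 points
- assumed risks 40% and 70%: 0.207 × 0.30 = 6.2 points
- assumed risks 30% and 70%: 0.207 × 0.40 = 8.3 points

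**4. Against the sampling error.** The standard error of the risk difference at the planned rates is √[(0.548·0.452 + 0.20·0.80)/29] = 0.119. The middle case is 6.2/11.9, about half a standard error.

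**5. What stratification would gain.** Simulation with 29 of 58 severe, control risks 40% and 70%, early-plasma risks 8% and 32% (averages 55% and 20%, close to the plan), and tests without continuity correction:

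| Randomisation | Test | Power |
|---|---|---|
| Unstratified | Chi-squared | about 79% |
| Unstratified | Cochran-Mantel-Haenszel | about 84% |
| Stratified | Cochran-Mantel-Haenszel | about 84% |

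Under these assumptions nearly all of the gain comes from the stratified test. Stratified blocks mainly guard against a visible imbalance, limiting the gap to about half a block per stratum.

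**6. What restricting the conclusion would cost.** If half the patients had PaO2/FiO2 above 300, that stratum would hold 14 to 15 per arm. With the full planned effect, the pooled formula gives power of 48% to 50%, against 79.8% for the whole trial.

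**The case against.** The strongest reply is that the trial is consistent on its own terms. The exclusion, the deferred-plasma trigger and the respiratory-failure outcome all use PaO2/FiO2 below 200, so no patient is past that line at entry. CALL serves only to select patients at higher risk; it is not the endpoint. This stands. A reader might infer that the trial mixes prevention with treatment of progression, or that the score tells nothing about a patient already at 200 to 300. The documents support neither reading. The first holds only under the footnote's definition. As to the second, the predicted state includes ventilation, which no enrolled patient needs at entry, and nothing shows that the score's items stop being prognostic in this range.

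Second, chance imbalance under concealed randomisation is not bias. It is part of the sampling error that the test and confidence interval already allow for. This also stands, and the 6-point shift should be read in that light.

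Third, the SAP allows adjustment for SOFA and imbalanced baseline variables, and blood gases are collected at baseline. This mitigates only in part. The analysis is exploratory, variables other than age and SOFA enter only once an imbalance has been seen, and SOFA is a multi-organ score rather than a direct measure of this split.

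Fourth, an unstratified design is a common choice in a small single-centre phase II trial. That is so; its absence is a missed improvement rather than an error.

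**Conclusion.** The point holds as a matter of precision and of protection against chance imbalance. Patients on both sides of PaO2/FiO2 300 are enrolled, and neither the allocation nor the primary test uses that information.

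The size is modest. A gap of 20 points or more has a chance of about 8 to 11% at the assumed shares tabulated (6 to 19% over all counts from 12 to 46). It would move the arm difference by about 6 points if the risks differ by 30. A stratified test would raise power by about 5 points under the assumptions simulated. All of this rests on an assumed severe share and an assumed risk difference.

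A reader might go further and infer that the primary result is biased, that the sample size is wrong for this reason, or that a prevention claim belongs only to patients above 300. None of these follows. Concealed randomisation keeps the comparison valid, the planned 29 per arm is reproduced, and restricting the claim would cut power to about half on the assumption that half the patients are in that stratum.

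**What to change.** 1. Use two block lists by baseline PaO2/FiO2, ≤300 versus >300. The exclusion criterion already requires this value to be known at enrolment, and blood gases are a baseline item. It is a more reproducible factor than saturation, because the footnote does not say whether SaO2 is on room air or on oxygen.
2. Make the primary test stratified (for example Cochran-Mantel-Haenszel) or adjusted for that factor. The resulting odds ratio is a within-stratum quantity and need not equal the crude one, so report both and name the primary one.
3. Report the primary outcome by stratum descriptively, with an interaction estimate and its confidence interval. Keep the conclusion for the whole randomised population.
4. State in the protocol how the CALL definition of severe disease relates to the trial's own line at 200, so that the two uses of progression are reconciled.

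If enrolment is too far on for new lists, items 2 to 4 can still be fixed before outcome data are seen by arm, and they keep most of the gain.

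Cost: one more item to enter at randomisation, a few lines of text, and stratum estimates that will be imprecise. The planned total of 58 does not change.

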**Randomization**

Eligible patients will be randomly assigned via computer generated numbering by a block randomization sequence into two groups: early or deferred plasma transfusion. Randomization will be done by an independent member and sequence will be concealed to study investigators.

**Convalescent plasma donation protocol**

Plasma will be obtained from volunteer patients who have recovered from COVID-19, having been asymptomatic for at least 28 days, with a negative SARS-CoV-2 RT-PCR in nasopharyngeal swab and in plasma, and anti-SARS-CoV-2 (S1) IgG titers ≥ 1:400 (Elisa Euroinmun). Given that for the Euroimmun SARS-CoV-2 IgG ELISA, a positive assay (defined as a ratio of sample optical density [OD]/calibrator OD ≥ 1.1) is determined—as per the provider—with a basal dilution of 1:100, we decided to further semi-quantify the IgG in donor plasma with an additional fourth fold dilution, and established the 1:400 cutoff as the requirement for our plasma donors (considering again an OD ratio ≥ 1.1 as a positive result for that new dilution).

A sample of plasma will be cryopreserved in order to measure neutralizing antibodies titers later, as described below. Only male or nulliparous female donors will be included to avoid the risk of anti-HLA/HNA/HPA antibodies. Donor plasma will be tested for standard infectious diseases before administration (hepatitis B virus, hepatitis C virus, HIV, HTLV I/II, *Trypanosoma cruzi* and *Treponema pallidum* serologies, as well as NAAT for HIV, hepatitis B, and hepatitis C viruses). Extracted plasma will be immediately frozen at -20°C according to standard national safety measures.^2^

**SARS-CoV-2 RT- PCR:**

Nucleic acids for SARS-CoV-2 detection from plasma and nasopharyngeal samples will be automatically extracted using MagNA Pure System (Roche) accordingly to manufacturer’s instructions. Reverse-transcription polymerase chain reaction (RT-PCR) will be performed targeting SARS-CoV-2 RdRP gen, using LightMix 2019-nCoV Real-time RT-PCR kit (TibMolBiol) and LightCycler 480 (Roche) for amplification. A threshold cycle (CT) above 35 will be interpreted as an indeterminate^3^.

**Anti-SARS-CoV-2 IgG ELISA**

For specific IgG enzyme-linked immunosorbent assays (ELISA) we will use the commercial kit CE-marked Euroimmun (Lübeck, Germany, # EI 2606-9601 G), which uses the S1-domain of the spike protein of SARS-CoV-2 as antigen. Fresh or thawed serum samples will be first diluted at 1:101 as is recommended by the instructions, then 2-fold serial dilutions will be done until 1:6400. The following step will be followed according to the manufacturer's protocol. Samples' immunoreactivity will be measured at an optical density (OD) of 450 nm (OD450). Results will be expressed as a ratio between OD of patients’ sample and OD of the calibrator provided with each ELISA kit. The quantitative results obtained will be interpreted as follows: OD ratio: <0.8 = seronegative; ≥0.8 and < 1.1 = indeterminate; ≥1.1 = seropositive. The end-point dilution will be determined for each sample as the final dilution where the OD ratio (patient/calibrator) is ≥1.1. Seroconversion will be defined as seronegative at baseline and seropositive after 3 or 7 days or, a 4-fold increase in end-point dilution titer from the baseline.

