**Statistical Analysis Plan**

Continuous variables will be shown as mean and standard deviation for normally data or median and interquartile range elsewhere. Categorical variables will be shown as the number of cases and percentages

Primary outcome

We will assess the effect of early plasma compared to delayed plasma on the primary binary outcomes through chi-squared tests or Fisher’s exact test when appropriate, and odds ratios will be presented together with 95% CI and p-values. In addition, as an exploratory analysis we will adjust for age and SOFA score at enrolment, and clinically significant baseline variables if they result imbalanced between both study arms, as fixed (individual-level) effects, using logistic regression. Values of p<0.05 (2 tails) will be considered.

Secondary outcomes

We will assess the effect of early plasma compared to delayed plasma on the secondary binary variables through chi-squared tests or Fisher’s exact test when appropriate. For continuous variables with normal distribution we will use the t-test, and for continuous variables with non-normal distribution the Wilcoxon-rank-sum test or Mann-Whitney U test for comparisons. Additionally, we will analyze binary variables using logistic regression. Numerical variables will be examined using generalized linear models with log link function and gamma family function. Treatment effects, crude and adjusted, will be presented as exponentiated coefficients, i.e. odds ratios, hazard ratios or incidence rate ratios, respectively and treatment effect estimates will be presented with 95% CI.

To test difference between Kaplan-Meier estimates in survival analysis, we will use the Log-Rank test and/or Cox proportional hazard models for time-to event variables.

For the analysis of paired continuous variables, we will use Wilcoxon matched-pairs signed-rank test.

Statistical significance will be defined using a 2-sided significance level of α = .05.

Immune response subgroup analysis

A pre-planned analysis of baseline neutralizing antibodies titers and anti-SARS-CoV-2 IgG titers progression (on days 0, 3, 7), is planned for participants from the early plasma group and for the subset of participants from the deferred plasma group who will not have yet received plasma on those scheduled days. Groups will be compared through Chi-squared tests or Fisher’s exact test when appropriate.

Statistical significance will be defined using a 2-sided significance level of α = .05.

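### The seroconversion rule does not separate donor IgG from the patient's own, so the early-versus-untransfused IgG comparison should be labelled and analysed as total circulating antibody, not as host response

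*Combined protocol and SAP*

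**What the plan says.** - **Rule.** The Anti-SARS-CoV-2 IgG ELISA section states: "Seroconversion will be defined as seronegative at baseline and seropositive after 3 or 7 days". The alternative route is "a 4-fold increase in end-point dilution titer from the baseline". Neither route mentions transfusion.
- **Assay in recipients.** The kit is one "which uses the S1-domain of the spike protein of SARS-CoV-2 as antigen". On the starting dilution: "Fresh or thawed serum samples will be first diluted at 1:101". An OD ratio of 1.1 or more is seropositive, and two-fold dilutions then run to 1:6400.
- **Plasma.** The donation protocol requires "anti-SARS-CoV-2 (S1) IgG titers ≥ 1:400", measured with the same manufacturer's ELISA, and sets no upper limit.
- **Exposure.** Intervention and comparison specifies "a total of 400 mL of ABO compatible convalescent plasma", given as two units 24 hours apart. The early arm starts on the day of enrolment. The deferred arm is transfused only on respiratory worsening, or if still hospitalized for symptomatic disease more than 7 days after enrolment.
- **Sampling.** Data collection schedules IgG titres on days 0, 3 and 7.
- **Comparison.** In the Statistical Analysis Plan, the Immune response subgroup analysis covers IgG titre progression in the early arm and "for the subset of participants from the deferred plasma group who will not have yet received plasma on those scheduled days". The only tests listed for it are chi-squared and Fisher's exact.

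**The concern.** Both units are scheduled before the day-3 sample. From then on, one comparison group carries infused antibody to the antigen being measured, and the other by design carries none. No section subtracts the infused amount, measures a marker that plasma does not supply, or limits the reading to total circulating IgG.

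If the ELISA rule is followed exactly, donor antibody can count as seroconversion. Reported under an immune-response heading, a significant difference could be read as plasma improving the patient's antibody response. The same mechanism could hide a weakened host response behind infused IgG. The planned data would support neither conclusion.

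**Working it through.** **Which endpoint is compared.** The analysis section names titre progression, not seroconversion. However, chi-squared and Fisher tests need a categorical endpoint, and seroconversion is the only category of IgG change defined. It is the likely endpoint, by inference.

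**Plan's own figure.** There is none to reproduce. The plan gives no expected rate, power or sample size for this comparison; the 29 per group was calculated for the primary composite.

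**Direction.** Take patients seronegative at baseline with the same true host rate p in both groups. Let q be the share of host non-converters pushed over the cut-off by infused IgG. The early-arm rate is then p + (1 − p)q, against p in the untransfused group. The difference, (1 − p)q, is never negative.

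**Infused contribution.** From the documents: volume 0.4 L, donor titre at least 1:400, first dilution 1:101. Assumed: plasma volume (PV) 2.5-3.5 L, titres that add linearly, and either none or half of the infused IgG lost from the circulation by sampling.

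Added titre = donor titre × 0.4/(PV + 0.4). The fraction is 0.4/2.9 = 0.138 at 2.5 L and 0.4/3.9 = 0.103 at 3.5 L.

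| Donor titre | Added, no loss | Added, half lost |
|---|---|---|
| 1:400 | 1:41 to 1:55 | 1:21 to 1:28 |
| 1:1600 | 1:164 to 1:221 | 1:82 to 1:110 |
| 1:3200 | 1:328 to 1:441 | 1:164 to 1:221 |

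**Donor titre at which infused IgG alone reaches 1:101.** This is 101 × (PV + 0.4)/0.4.

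- No loss: 101 × 2.9/0.4 = 732 to 101 × 3.9/0.4 = 985.
- Half lost: 1464 to 1969.

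**The 4-fold route.** A patient already at 1:101 needs about 404 − 101 = 303 more. That takes a donor titre of 303 × 2.9/0.4 = 2197 to 303 × 3.9/0.4 = 2954 with no loss, or about 4394 to 5909 with half lost. Patients already seropositive at baseline are thus much harder to convert by infusion.

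**Tipping at the 1:400 minimum (illustration only).** Trials of 29 versus 29 were simulated 1,500 times per setting. Assumptions: PV 3.0 L; everyone below the cut-off at baseline (uniform 0 to 70); the same log-normal host rise in both arms (median 60, log-scale SD 1.5); no deferred patient transfused.

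| Donor plasma | Early arm | Deferred arm | Fisher p < 0.05 |
|---|---|---|---|
| No donor IgG | about 49% | about 49% | 2-3% |
| 1:400, half lost | 62% | 49% | 12% |
| 1:400, no loss | 79% | 49% | 59% |

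The host distribution is invented. The simulation shows that the mechanism operates even at the minimum titre; it does not estimate its size in this trial.

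**The case against.** The strongest reply is that the plan never claims to measure the patient's own response. The Subgroup analysis section openly contrasts patients given immediate plasma with patients given none, which fits a study of antibody exposure. The specific objectives are clinical progression, safety and viral clearance; host antibody response is not among them. The analysis section does not name seroconversion. The only donor titre documented is the 1:400 minimum, which cannot convert an IgG-negative patient alone. With up to 7 days of symptoms allowed, some patients may be seropositive on day 0 and must meet the harder 4-fold route. Baseline-indeterminate patients do not meet the first route at all.

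All of this stands, and it rules out three stronger readings that a reader might infer:

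- that the plan states a host-response claim: no section does;
- that the plan explicitly prescribes a seroconversion test between groups: that is inferred from the tests listed;
- that the rule necessarily misclassifies the early arm, or does so by a calculable number of percentage points: this depends on donor titres, baseline serostatus and IgG loss, which the documents do not give.

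What does not stand is that nothing needs changing. The term seroconversion, an immune-response heading and categorical tests together invite the host-response reading, and no sentence in the plan blocks it.

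**Conclusion.** The point holds as a matter of labelling and analysis choice. Followed exactly, the rule can produce a between-group difference when host responses are identical, or conceal a reduced host response. The direction of the distortion follows from the documents: same antigen, infusion scheduled before sampling, and an untransfused comparator. Its size does not. It rests on the assumed plasma volume of 2.5-3.5 L, additive titres, the share of infused IgG lost, and a donor titre distribution of which only the minimum is stated.

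Severity is minor. One immunological subgroup analysis is affected; the primary outcome, the listed secondary outcomes, safety and the sample size are not.

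**What to change.** 1. **Anti-SARS-CoV-2 IgG ELISA.** State that seroconversion is not interpreted as host response in any sample taken after plasma. On days 3 and 7 this covers the whole early arm.
2. **Immune response subgroup analysis, label.** Rename the IgG comparison as total circulating anti-S1 IgG (donor plus own), a measure of antibody exposure.
3. **Immune response subgroup analysis, method.** Compare end-point titres on days 3 and 7 with a between-group difference or ratio and 95% CI, in place of a chi-squared or Fisher test of seroconversion. State how results below 1:101 or at the 1:6400 limit are entered.
4. **Comparator.** Note that the untransfused deferred subset is selected after randomization. The prolonged-stay criterion applies only after day 7, so up to then the rule removes those who met the respiratory-worsening criterion. Relabelling does not cure this, so the comparison should be called descriptive.

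The samples, assay and treatment stay the same. The cost is a few sentences, and the trial gives up only a host-response claim it could not support.
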